### Main endpoint

This study's main endpoint is a major osteoporotic fracture that occurs during the follow-up period of the study. Major osteoporotic fracture is defined as a new fracture of the hip (not present at the time of recruitment), a clinical fracture of the vertebrae or a proximal fracture of the humerus or wrist. Fractures derived from severe traumatism (traffic accidents, collisions, gravitational trauma) will not be included, nor will pathological fractures due to other causes (bone cancer, metastasis to the bone, and Paget's disease established through diagnosis).

### Secondary endpoints

The study also contemplates two secondary endpoints: osteoporotic fracture of the hip and mortality due to any cause.

### Other variables

The independent variables used in this study were selected after reviewing the literature and current practice guidelines, and includes the patient's age, gender, weight and height with a calculation of the BMI, smoking habits, drinking habits, exercise habits, history of parental hip fracture, low calcium intake, untreated hypogonadism in men or women, rheumatoid arthritis, other metabolic bone diseases excluding hypogonadism, use of oral glucocorticoids, use of drugs affecting bone metabolism other than glucocorticoids, previous osteoporotic fracture, high risk of fall, prolonged immobilization, densitometric osteoporosis of the lumbar spine established through DXA (T score for L2-L4), densitometric osteoporosis of the hip established through DXA in the total hip or the femur neck (T score) and treatments for osteoporosis. The participating physicians will be trained in the management of these variables and will be given a procedures manual containing all pertinent definitions. Information about antiresorptive treatment will be collected from the GAIA system, the electronic prescription system associated with the ABUCASIS that currently covers 95% of all prescriptions dispensed in the Region. It records all the information about the drug prescribed, along with its dosage and the length of treatment.

### Development of the study

Milestones of the study included: the selection and training of the participating clinicians, the selection of patients, the cohort baseline data analysis, the preliminary analysis and the analysis at the end of the follow up period (figure 1).

**Figure 1 F1:**
[figure not shown]
**Flow diagram of the study**.

#### Selection and training of the participating clinicians

Approximately 800 clinicians will be selected for participation (family doctors and nurses) from the 23 Health Departments in the Region of Valencia which have implanted the ABUCASIS system and chose to participate voluntarily in the study. In order to stimulate involvement in ESOSVAL, the Valencia Health Agency have incorporated the participation in the study into the governance contract with the Health Departaments, and linked it to the existing system of economic incentives associated to quality indicators.

#### Selection of patients

Patients will be recruited through the participating primary healthcare centers over a 18-week period. The clinicians will select 36 patients opportunistically as they attend the medical practices, distributing them for every day of the week and according to the healthcare centers different schedules. The minimum recommended recruitment frequency is two patients per week, for the 18-week period until reaching 36 recruits with the profile (age and sex) that has been assigned to each participating clinician by the research group.

#### Follow-up

In order to develop the scales necessary to meet our research goals, follow-up must be long-term, between five to ten years, so that a high enough number of hip fractures have occurred for analysis to be significant (a fracture in any other location is much more frequent and does not require as long a follow-up period as contemplated in this study). During the initial medical visit, information will be collected and/or completed concerning all of the variables that will be used in the calculation of the risk of osteoporotic fracture. During the follow-up period, the research group will keep an exhaustive record of all new fractures, consulting all of the Valencia Health Agency's available information systems to do so. At five years (and if the researchers decide to extend the study, at ten years) the variables explored during the initial visit with the clinician will be reviewed. The fieldwork will begin in 2010, and be completed in 2015; it will be extended to 2019 if necessary.

### Ethical aspects

The study will be conducted according to the international standards of the International Guidelines for Ethical Review of Epidemiological Studies (Council for International Organizations of Medical Sciences-CIOMS-Geneva, 1991) and the recommendations of the Spanish Society of Epidemiology about the review of ethical aspects of epidemiological research.

The ESOSVAL-R study has been reviewed and approved by the Committee for Ethics and Clinical Trials of the Center for Public Health Research. The ESOSVAL-R is a naturalistic, observational study undertaken as part of routine clinical practice, with no intervention (apart from training of participating clinicians) with the patients included in the study. No additional risks associated with participation are anticipated, as no additional diagnosis, evaluation or treatment will be provided, apart from what the attending physician deems appropriate.

#### Confidentiality of the data

All information relative to the patients' identity will be considered confidential to all effects. Data concerning patients that is collected from the ABUCASIS system during the study will be documented anonymously, making impossible to use this information to identify the patients. The only connection between these data and the patient will be a simple code used exclusively for this study, in such a way that only the ABUCASIS system will be able to associate the data to an identified or identifiable individual. The data generated during the study will be handled as stipulated in the Law 5/1999 and corresponding norms. All of the researchers with access to the data used in the study will be required to sign a document guaranteeing confidentiality.

#### Informed consent

Although the study does not involve the randomization of the sample or the application of further interventions, prior to inclusion, all patients must read the "Patient Information Form" and sign a document giving consent, and granting the researchers access to information contained, in an anonymous way and only for the purposes of this study, in their clinical records.

### Statistical analysis

Once the recruiting process has been completed, the cohort baseline data will be analyzed. A description will be made of the patients' characteristics along with their current risk factors. The analysis will be stratified by five-year age-sex subgroups. The appropriate parameters (means, proportions) will be used with each variable with their corresponding 95% confidence intervals (CI95%). A bi-variable analysis will also be made to evaluate the relationships between risk factors that are of most interest. Simple Odds Ratios (OR) will be applied to estimate the strength of association and, when necessary, multiple logistic regression models will be used.

At two and five years of follow-up, an analysis will be made of the strength of association between the risk factors and the incidence of osteoporotic fracture in all locations and in the hip. For this, bi-variable analysis and Cox' proportional hazards models will be used. Additionally, a specific model will be developed to analyze the probability of death once a fracture has occurred (controlling for the effect of the different types of fractures).

Next, the most parsimonious of Cox' proportional hazards models will be applied to two-thirds of the sample (approximately 10,000 subjects randomly selected) to develop a scale to predict the risk of osteoporotic fracture. The scale's prediction capacity will be evaluated with the C statistic, and its calibration will be evaluated with the Hosmer-Lemeshow test, or a similar test. The predictive weights of the risk factors obtained in this model will be applied to the remaining third of the database (approximately 5,000 subjects) to evaluate whether prediction capacity (C statistic > 0.75) and calibration (non-significant Hosmer-Lemeshow test) are maintained. Scaling techniques will then be applied to construct a simplified scale on the basis of the validated model.

Finally, the calibration and the capacity for discrimination of the FRAX scale will be evaluated in the population of the Region of Valencia, Spain. If necessary, the FRAX will be recalibrated to make it more appropriate for the population in question. This time, the weights of the original scale will be used in conjunction with the incidence of osteoporotic fracture derived from our study. If the scale shows poor prediction capacity (statistics < 0,75), or if it is not correctly calibrated, it will be recalibrated with the weights derived from our own scale.

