The most recent score for estimating the individual risk of osteoporotic fracture or hip fracture over 10 years has been developed by Hippisley-Cox et al [24] in the UK population. These new risk prediction algorithms (QFractureScores) for osteoporotic fracture and hip fracture do not require laboratory measurement and so can be used in primary care or for individual self assessment. The validation statistics, especially for the hip fracture algorithm, suggest that the QFractureScores are likely to be useful for identifying patients at high risk of fracture in the primary care setting in the UK and showed improved performance compared with FRAX.

The main implication of these results is that when developing a scale for a specific population, or recalibrating an international scale to the fracture incidence of a given country, local data must be collected. Local studies will focus on a highly heterogeneous population that represents the real risks of a given region, and will help to establish osteoporosis treatment thresholds.

The Valencia Health Agency, the public healthcare network that covers close to 93% of the inhabitants of the Region of Valencia, has implanted an electronic medical record system called ABUCASIS. This population-based electronic database allows carrying out longitudinal studies of all the patients attending the healthcare centers from the Region of Valencia, enabling the monitoring of most relevant clinical data. It is now possible to do a low-cost cohort study that will ultimately lead to developing a risk scale with a 5-10 year window for patient follow-up.

The main objective of the ESOSVAL-R is to develop a risk prediction scale of osteoporotic fracture using data from the Region of Valencia. This scale will allow identifying intervention thresholds to support treatment decision-making in the Valencia setting, based mainly on the information registered in the electronic clinical records.

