### Specific objectives

1. To describe baseline characteristics of the cohort under study and the prevalence of risk factors for osteoporosis. This objective will reveal the current prevalence of risk factors for osteoporosis in men and women over 50 years in the Region of Valencia.

2. To evaluate the strength of association between risk factors and the incidence of osteoporotic fracture at five years for the overall population over the age of 50, and for the five-year age-sex subgroups. This objective will also be developed specifically for the risk of hip fracture.

3. To analyze using survival models the time relationship between risk factors and the incidence of osteoporotic fracture and the risk of hip fracture.

4. To identify in patients with osteoporotic and hip fracture factors of poor prognostic for survival.

5. To develop and validate a prediction scale for the risk of osteoporotic fracture at five years, specific to the population of the Region of Valencia, Spain.

6. To evaluate the calibration and the discrimination capacity of the FRAX scale in the population of the Region of Valencia and, if necessary, to recalibrate this scale for its use in the Valencia population.

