### Data sources

The main source of data will be the ABUCASIS electronic clinical records. For the outcome variables, this source will be completed with hospital morbidity records (Discharge Data sets and other systems being implanted), hospital accident and emergency records, and the regional Ministry of Health's mortality registry. Baseline data, including the patient's risk factors at the time of recruitment into the cohort, will be collected during the initial visit, using a new modified version of the ABUCASIS specifically developed to collect information about the variables used in the study that were not routinely found in clinical records. The results of previous exams (x-rays or densitometry) that may have been performed on the patients will be included in the initial evaluation (information about previous fractures and densitometry values). In the case of densitometry results, the information that will be included in the initial evaluation will be from examinations done in a period of ± 2 years at the time of recruitment.

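### The five-year fracture-risk scale is built from an ordinary Cox model in which death before fracture has no stated role; used in the ordinary way, that model overstates absolute risk, mainly in the oldest

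*Protocol article*

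**What the plan says.** All places are in the protocol article.

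- **Target.** Specific objectives, item 5: "To develop and validate a prediction scale for the risk of osteoporotic fracture at five years". This is an absolute risk over a fixed horizon.
- **Use.** Background: "This scale will allow identifying intervention thresholds to support treatment decision-making in the Valencia setting". The end of the Discussion adds that, with later cost-utility work, the scale should help set the risk level for starting treatment.
- **Model for the scale.** Statistical analysis: "the most parsimonious of Cox' proportional hazards models will be applied to two-thirds of the sample", the purpose being "to develop a scale to predict the risk of osteoporotic fracture". The weights are then applied to the remaining third, with a C statistic and a Hosmer-Lemeshow or similar test, and a simplified scale follows.
- **Model for association.** In the paragraph before, for the two-year and five-year analyses: "bi-variable analysis and Cox' proportional hazards models will be used".
- **Death.** The secondary endpoints are "osteoporotic fracture of the hip and mortality due to any cause". Data sources include "the regional Ministry of Health's mortality registry". The only model that involves death is in Statistical analysis: "a specific model will be developed to analyze the probability of death once a fracture has occurred". It starts at the fracture, so it does not cover deaths that prevent one.
- **Population.** Age 50 and over, with no upper limit stated (Population and sample).

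The article does not mention competing risks, a censoring rule for death or a cumulative incidence function. It does not say how the Cox weights become an absolute risk. The list of biases in the Discussion does not include competing mortality.

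**The concern.** A patient who dies without a fracture can no longer have one. If such patients are treated as censored, one minus the Cox survival estimates the fracture risk in a hypothetical population in which nobody dies first. For hazard ratios this does no harm, because a cause-specific Cox model is a proper tool for strength of association. For an absolute risk compared with a threshold it is the wrong quantity, and it errs in one direction only: upwards.

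The error grows with mortality, hence with age and frailty. A single rescaling of the whole scale would not remove it, because younger patients need almost no correction and the oldest need the most. Patients near a threshold in the highest age groups would be placed above it more often than their real risk warrants. The same incidence also feeds the FRAX recalibration, which uses the fracture incidence found in this study, so the error could pass into that product.

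**Working it through.** **1. The plan's own figure.** The article gives no predicted risk and no mortality, so there is no figure on this exact point to reproduce. The nearest is the sample size for hip fracture (Population and sample), with two-sided alpha 0.05, power 0.80, SD 0.75, hazard ratio 1.33, squared multiple correlation 0.10, five-year incidence 15 per 1,000 and losses of 10%:

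- events = (1.960 + 0.842)² / [0.75² × (ln 1.33)² × (1 − 0.10)] = 190.6
- N = 190.6 / 0.015 / 0.90 = 14,121.3, which rounds up to the stated 14,122.

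The sample size is reproduced and does not depend on the point made here. It does supply one fracture rate: 15 per 1,000 over five years is about 0.003 per year.

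**2. Inputs for the check.**

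- Fracture hazard f: 0.003 per year (from the sample-size assumption); 0.005 to 0.007 per year (Background, hip fracture over age 60); 0.02 per year (an assumption for the oldest, not in the documents).
- Death hazard before fracture, m: not in the documents; assumed from 1% to 15% per year.
- Horizon t: five years (Specific objectives, item 5).

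**3. Formulas, constant hazards.**

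- Risk with deaths censored: 1 − exp(−f t)
- Risk with death competing: f/(f + m) × [1 − exp(−(f + m) t)]

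**4. One line in full.** For f = 0.007 and m = 0.10:

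- censored: 1 − exp(−0.035) = 3.44%
- competing: 0.007/0.107 × [1 − exp(−0.535)] = 2.71%
- ratio: 1.27.

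**5. Results at five years** (risk with death competing; ratio of censored to competing risk in brackets).

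| m per year | f = 0.003 (censored 1.49%) | f = 0.007 (censored 3.44%) | f = 0.02 (censored 9.52%) |
|---|---|---|---|
| 1% | 1.45% (1.03) | 3.36% (1.03) | 9.29% (1.02) |
| 3% | 1.38% (1.08) | 3.20% (1.08) | 8.85% (1.08) |
| 5% | 1.32% (1.13) | 3.05% (1.13) | 8.44% (1.13) |
| 10% | 1.17% (1.27) | 2.71% (1.27) | 7.52% (1.27) |
| 15% | 1.05% (1.42) | 2.42% (1.42) | 6.74% (1.41) |

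For f = 0.005 and m = 0.02 the ratio is 1.05, so mortality of 2-3% per year gives 5-8%.

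**6. Reading the table.** Across a row the ratio hardly changes, so the relative error is set by mortality and time and not by the fracture rate. In absolute terms, at f = 0.007, the gap is 0.08 percentage points at m = 1% and 0.73 to 1.01 points at m = 10-15%. At the assumed f = 0.02 it is 2.00 to 2.78 points at m = 10-15%.

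**7. Sensitivity.** If the death hazard rises 9% per year during follow-up from a start of 10% or 15%, with f = 0.02, the five-year ratios are 1.31 and 1.48. Constant hazards do not exaggerate the effect.

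**The case against.** The strongest reply is that the article does not say what the concern supposes. A reader might infer that the plan censors deaths and reads risk as one minus the Cox survival. Neither statement appears. A Cox model for fracture can be combined with one for death into a valid cumulative incidence, and a fuller document that is not shown might say so. This stands, and the point is therefore conditional on ordinary use. It does not dispose of the point. The section fixes the model, the split, the performance criteria and even a separate model for death after fracture, yet gives death before fracture no role in a scale meant for absolute risk.

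Second, the association sentence is no evidence of a fault, since Cox regression is suitable there. That stands; the point rests on the scale-building sentence.

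Third, the large figures need high mortality, which is assumed, as is the 2% fracture rate. At the documented rate over age 60 with 2-3% mortality, the gap is only about 0.1 to 0.25 percentage points. Excluding people who cannot attend their centre may lower mortality in the cohort, although the Discussion also warns that the very old or sick may be over-selected. The net effect is unknown. The fracture rates used are also for hip fracture, a secondary endpoint. This matters little for the relative error, because the ratio barely moves with f.

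Fourth, a reader might infer that the calibration test could not detect the error, or might extend the figures to ten years. The documents support neither. If observed risk is the crude proportion with a fracture, over-prediction could show; if deaths are censored there too, it would not; the article does not say which. Ten-year follow-up is only an option, and the planned scale is for five years.

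**Conclusion.** The point holds in conditional form. The article names an ordinary Cox model as the only basis for a five-year absolute-risk scale and assigns no role in it to death before fracture. If that model is used in the ordinary way, the scale overstates risk. The direction is certain under that use. The size rests on assumed mortality and constant hazards: about 3% relative at 1% mortality per year, 5-8% at 2-3%, and roughly 27-42% at 10-15%. For most of the cohort it would probably be minor. For the oldest it could be material, and the intended threshold use makes that group the one to protect.

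The documents do not support saying that the plan has chosen to censor deaths, or that the finished scale will be wrong by a known amount. The association analyses and the sample size are unaffected.

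**What to change.** - Keep Cox hazard ratios for the association objectives.
- For the scale, state that absolute risk is the five-year cumulative incidence of fracture with death as a competing event. Obtain it by combining cause-specific Cox models for fracture and for death, or from a Fine-Gray model.
- Assess calibration against observed incidence from the Aalen-Johansen estimator, overall and by age group, so that an error confined to the oldest is visible.
- Use the same incidence when FRAX is recalibrated.

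**Cost.** The mortality registry is already a data source, so no new data collection is needed and the sample size does not change. The price is some more analysis code and a slightly more complex risk formula behind the simplified scale.

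### The written order of analyses most naturally lets the validation third help select the scale's predictors, and nothing sets that third aside first, so its C statistic may be slightly optimistic

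*Protocol article*

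**What the plan says.** The Statistical analysis section of the protocol article sets out the outcome work in this order:

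1. Association: "At two and five years of follow-up, an analysis will be made of the strength of association between the risk factors and the incidence" of fracture at all sites and at the hip, by bi-variable analysis and Cox models. No subsample is named. Under Specific objectives, objective 2 places this work "at five years for the overall population over the age of 50, and for the five-year age-sex subgroups".
2. Development: "Next, the most parsimonious of Cox' proportional hazards models will be applied to two-thirds of the sample", about 10,000 people chosen at random. This is the first mention of a split.
3. Validation: the weights are carried to the other third, about 5,000 people, to see whether "prediction capacity (C statistic > 0.75) and calibration (non-significant Hosmer-Lemeshow test) are maintained".

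The Abstract keeps the same order: association analysis is item 2, and model development and validation is item 3. On candidates, the Other variables section says: "The independent variables used in this study were selected after reviewing the literature and current practice guidelines". It lists about 20. The article does not say on which data the parsimonious model is selected, or that the validation third is held back while outcomes are examined.

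**The concern.** A held-out third gives independent evidence only if its outcomes played no part in building the model. Here the weights are held out, but the choice of predictors may not be. A predictor that happens to do well in the validation third would be more likely to enter a model selected on everyone, and would then be credited again when C is measured in that third. This is a separate matter from how large the third is.

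The main objective is to develop and validate a scale, and this check is the only validation described for it. A pass leads to the simplified scale. The same section also lets the study's own weights be used to recalibrate FRAX if FRAX falls below 0.75. FRAX was not selected on these data, so a common bar of 0.75 would slightly favour the study's own scale.

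**Working it through.** **The plan's own figure.** The inputs are in Population and sample: alpha 0.05 (two-sided reproduces the stated N), power 0.80, SD 0.75, squared multiple correlation 0.10, hazard ratio 1.33, incidence 15 per 1,000, losses 10%.

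- Events: D = (z for alpha + z for power)² / (SD² × (ln HR)² × (1 − R²)) = (1.960 + 0.842)² / (0.5625 × 0.0813 × 0.90) = 190.6
- N followed = 190.6 / 0.015 = 12,709
- N recruited = 12,709 / 0.90 = 14,121, against 14,122 stated

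This gives the simulation setting: about 12,710 people followed and about 191 hip fractures. (The article states 180 expected hip fractures.) The article gives no incidence for major osteoporotic fracture. An assumed 5% gives 12,710 × 0.05 = about 635 events.

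**Simulation of the two readings.** A logistic model at five years stands in for the rare-event Cox model. Predictors are chosen by backward elimination at 0.05, either in the whole cohort or in the two-thirds only. In both cases the weights are fitted in the two-thirds and C is measured in the third. The tabulated quantity is whole-cohort minus development-only selection, paired within replicate.

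| Set | Candidates | Hip, about 191 events | Major fracture, about 635 events (assumed) |
|---|---|---|---|
| A, 100–200 replicates | 22, of which 7 real | 0.0069, 0.0092, 0.0084 (SE 0.0007–0.0011) | 0.0039, 0.0023 (SE 0.0002–0.0004) |
| B, 40–60 replicates | 20 | 0.0094 (SE 0.0011) | 0.0031 (SE 0.0005) |
| B, 40 replicates | 40 | 0.0156 (SE 0.0020) | not run |
| C, 80 replicates per pattern | 20, three effect patterns | 0.012–0.020 | 0.001–0.002 |

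Set A reports the difference in validation C. Set B reports the difference in optimism, that is, validation C minus C in a large independent sample. For hip with 20 candidates in set B:

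- whole-cohort selection: 0.7332 − 0.7219 = 0.0113
- development-only selection: 0.7210 − 0.7190 = 0.0019 (rounded from unrounded values)
- excess: 0.0113 − 0.0019 = 0.0094

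**Against sampling noise.** The SD of validation C was about 0.03 for hip and 0.016 to 0.019 at 5% incidence. The bias is therefore roughly 0.001/0.019 = 0.05 to 0.004/0.016 = 0.25 SD for major fracture, and 0.007/0.03 = 0.23 to 0.020/0.03 = 0.67 SD for hip.

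**Chance of passing 0.75.** In set A, with true C near 0.745, the pass rate rose from 32% to 36% (635 events) and from 34% to 45% (191 events). As a check, on the normal scale these are moves of 0.47 − 0.36 = 0.11 SD and 0.41 − 0.13 = 0.28 SD. They correspond to shifts in C of 0.11 × 0.016 = 0.002 and 0.28 × 0.03 = 0.008, in line with the table.

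**The case against.** The strongest reply is that the article never says the predictors are chosen on the whole cohort. The development step uses "approximately 10,000 subjects randomly selected) to develop a scale to predict the risk of osteoporotic fracture", which can mean that parsimonious modelling takes place inside the two-thirds; the split would then be clean. *Next* may only order topics, as *Finally* does for FRAX. Objective 2 concerns association, for which the full cohort is right; the scale is objective 5. Candidates come from literature and guidelines, and the weights are held out. Which data and rule are used for selection is often left to an analysis plan.

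Much of this stands. A reader might infer that the plan prescribes whole-cohort selection, or that its validation is void; the documents support neither. A reader might also infer that calibration will look too good, but only C was computed. Nor should the hip figures lead, because the main endpoint is major osteoporotic fracture and hip fracture is secondary.

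What the reply does not remove is the stated order. Picking the most parsimonious *of* the Cox models implies a choice among models, and the only fracture-incidence Cox models described before that point are the association models. Even if selection is repeated inside the two-thirds, the study will by then have seen every predictor's association in everyone, with nothing barring its use. The article itself sets the sequence, the split and the pass mark, so this is more than detail left to another document.

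**Conclusion.** The point holds as a weakness in the stated sequence, with medium confidence. Followed as written, the plan most naturally allows events in the validation third to influence which predictors enter the scale, and it contains no safeguard against this. If that happens, validation C is biased upward by about 0.001 to 0.004 for major osteoporotic fracture and about 0.007 to 0.020 for hip fracture.

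These sizes rest on an assumed 5% incidence of major fracture, 20 to 40 candidates, assumed effect sizes, backward elimination at 0.05 and a logistic approximation. The bias is below the sampling SD of C and would matter mainly for a result close to 0.75. It is nevertheless systematic and favours passing. Its effect on the Hosmer-Lemeshow result is not quantified.

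**What to change.** In the Statistical analysis section:

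- Draw the random two-thirds/one-third split before any outcome association is examined, which means before the two-year analysis.
- Do all outcome-based screening and model selection for the scale in the two-thirds only. If resampling is used instead, repeat the full selection in every resample.
- Keep the two- and five-year whole-cohort association analyses for objectives 2 and 3 as scheduled, and state that they will not be used to choose predictors for the scale.

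This needs a few sentences, no further patients or data, and no loss of the two-year milestone. The cost is slightly less data for selecting predictors and a possibly slightly lower validation C. In set B, development-only selection lowered C in the large independent sample by 0.7219 − 0.7190 = 0.003 for hip with 20 candidates, and by 0.7291 − 0.7278 = 0.001 at 5% incidence.
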